### Study design

This intervention will take a quasi-experimental design approach with an experimental and control site. The project will involve pre- and post-intervention data collection with one comparison group to assess intervention effects.

The study will be conducted at level 4 and 5 hospitals, each hospital having high volume of clients and covering a sub-county, all with similar maternal, newborn and child health indicators. Five hospitals will be the implementation sites while 4 hospitals will be control sites in a step wedge approach. The implementation sites will be selected purposely. The control sites will receive the full intervention after 1 year when the first set of comparison with the intervention site has been completed.

The 5 experimental site hospitals will receive a set of interventions which include: refurbishing of new born units, installation of equipment such as incubators, respirators, Ambu bags, and radiators. Establishment of a tele-health platform to enable free flow of information amongst clinicians and obstetricians, establishment of a call center for follow up of patients, training of health care providers in neonatology, and creating awareness amongst the community will be key cross cutting interventions, implying they will benefit the intervention site as well as control site. The control sites will not receive the main intervention benefits (equipped specialized newborn units) until after 1 year of implementation in the experimental sites.

The project will undertake a baseline, mid-term and end-line surveys. The step wedge design which allows for the measurement of process, outcome and impact indicators within each site (at different time points) will be used. The design also allows a comparison between different combinations of the intervention components.

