### Primary outcome measure

Percentage reduction in newborn deaths in Bungoma County between October 2015 and December 2018. This will be measured by comparing the number of newborn deaths at the nine project facilities (in the period of implementation), with the number of deaths at the same facilities in the similar period before the intervention; converted to percentage and aggregated by facility.

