### Control group – Minimizing bias and contamination

To minimize bias and contamination, the intervention sites will be selected purposely from the nine county and sub- county hospitals. The sites selected will include the two facilities that have some level of neonatal facilities to ensure that the intervention sites and the control sites have distinct features separating the two.

We will measure the utilization of services in the selected facilities at baseline, mid-term and end-line levels.

To determine utilization of neonatal services, we will collect data directly from the source through a data abstraction form in the nine health facilities throughout the project period. Further, the community health workers and volunteers will also provide information of the number of cases they refer to specific facilities. Cases that fail to arrive at the health facilities will also be captured and the data from the facilities and the community health workers will be cleaned, cross checked and analyzed to provide required results for utilization of neonatal services.

Quality of care will be determined through observations of service provision by clinicians, as well as checking use of neonatal equipment and the severity of conditions managed by the health providers in the units.

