#### Rationale

The project will establish 7 new special care units and enhance capacity in 2. Following the 3 months module based competency based neonatology course for 90 health care workers in these units, it will be important to provide medical consultation support by pediatricians. This will facilitate timely clinical decision making including and not limited to; judicious use of medicines such as antibiotics, change of treatment, fluids administration, nutritional calculations, immunization decisions, evolution of diagnosis, need for referral and follow up strategies. This virtual support will build the clinicians confidence in clinical management of newborns, knowing that they can ask and get help at any time of the day, all week, ultimately improving outcomes.A major challenge for clinicians working in peripheral, rural areas in Kenya, has been keeping in touch with best care practices due to inability to access this information, lack of continuous education on how to apply the updates on best care and failure of follow up on adoption of best care practices. The telehealth platform will provide virtual best care practices updates service regularly and interactively. Pediatricians and the special units’ clinicians will be able to discuss on implementation of the updates, challenges they face and lessons learnt. This will promote free flow of information between the consultants and the clinicians, promoting best care practices and newborn outcomes.The telehealth platform will enable data collection on clinical challenges and gaps that will inform project evaluation, areas of emphasis in the continuous medical education and enhanced efficiencies in other processes such as call center follow up and referral systems.

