#### Operation-how the call center service will work

In order to support newborns’ mothers on checking on their babies’ health through follow up, we plan to use the following strategies:

For mothers who are able to read and write an sms, the call center attendant will send out an sms 3 times a week in the mothers best language of comprehension (e.g. Kiswahili, Kibukusu, Kisabaot etc.) prompting them to check and feedback on the following:Ability of the newborn to breastfeedSymptoms of dehydrationIrritabilityBreathing- ease or difficultyHotness or ‘coldness’ of body2.For mothers who are not able to read or write an sms, the call center attendant will make a call 3 times a week in the mother’s best language of comprehension prompting on the above a-e.3.In case responses following the above enquiries are not satisfactory (or point to a baby having a health problem) they shall be advised on immediate measures to take and referred to the special care units.4.Mothers will be able to initiate the sms or call in case they need any help or information.5.Immunization information will also be provided.6.Expectant mothers will be called or texted with messages promoting knowledge on newborn health such as exclusive breastfeeding, immunization, hygiene and danger symptoms.

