#### Control group

The study ensures that the control group will also receive the full intervention towards the end of the project period so that they do not remain disadvantaged. Initially they shall benefit from community sensitization, tele health platform and call center. After a period of 1 year, the control group will be ready for the full intervention which will include establishment of functional specialized neonatal units.

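### If the year-1 comparison between arms counts deaths at the treating hospital, call-centre referral out of control areas biases it against the intervention

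*Protocol article*

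**What the plan says.** Five statements in the protocol article combine to produce the problem.

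- **Referral.** Under the operation of the call centre, mothers whose replies suggest a sick baby are handled as follows: "they shall be advised on immediate measures to take and referred to the special care units". No restriction by arm or catchment is stated.
- **Who has the call centre.** The Control group section says of the control sites: "Initially they shall benefit from community sensitization, tele health platform and call center". Study design likewise treats the call centre, telehealth, training and awareness work as reaching both arms.
- **Where the units are.** Study design: "The control sites will not receive the main intervention benefits (equipped specialized newborn units) until after 1 year of implementation in the experimental sites". The section on minimizing bias and contamination adds, of the intervention sites, "The sites selected will include the two facilities that have some level of neonatal facilities".
- **How deaths are counted.** Primary outcome measure compares the number of newborn deaths at the nine project hospitals with a similar earlier period, and the result is "aggregated by facility".
- **When arms are compared.** Study design: "Five hospitals will be the implementation sites while 4 hospitals will be control sites in a step wedge approach". Control hospitals receive the full package after one year, once a first comparison with the intervention sites is complete.

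**The concern.** The referral path and the counting rule pull against each other in the one period when the control hospitals still lack units. A sick baby from a control catchment who is reached by the call centre is pointed to a unit and, in year 1, that unit is at an intervention hospital. If the baby dies there, a count by treating facility charges the death to the intervention arm. If the baby would otherwise have died in a control hospital, the control arm's count also falls.

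Either way the bias in deaths runs against the intervention, and it arises from following the plan as written. At stake is the only comparison with hospitals that do not yet have the units. The section on minimizing bias and contamination does not say to which arm a referred baby's death belongs.

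**Working it through.** **Step 1: do equipped units stand only at intervention hospitals in year 1?** The telehealth rationale says: "The project will establish 7 new special care units and enhance capacity in 2". That makes 7 + 2 = 9 units, one per project hospital. The two hospitals with existing neonatal facilities are among the five intervention sites, so 5 − 2 = 3 new units go there and 7 − 3 = 4 go to the control hospitals. Those four come only after a year. The count agrees with the text.

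**Step 2: size on raw counts.** The documents give no referral volume or fatality among referred babies. Assumptions: 50 deaths expected per arm in year 1, a true 30% reduction for any baby treated at a unit (the project's target), and R deaths expected among rerouted control-area babies.

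Intervention count = (50 + R) × 0.7. Control count = 50 − R if all are moved from control hospitals, or 50 if all come from the community and would have been counted at no project hospital.

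| R | Intervention | Control, all moved | Ratio | Control, all from community | Ratio |
|---|---|---|---|---|---|
| 0 | 35 | 50 | 0.70 | 50 | 0.70 |
| 5 | 38.5 | 45 | 0.86 | 50 | 0.77 |
| 10 | 42 | 40 | 1.05 | 50 | 0.84 |

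**Step 3: size on the protocol's own metric, percentage change per facility.** Assumptions: equal baseline deaths at each of nine hospitals, a 30% reduction at the five intervention hospitals, none at the four controls, and a fraction f of control-hospital deaths moved. Let m be the fatality of moved babies relative to what it would have been (1 = unchanged, 0.7 = also cut by 30%).

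Apparent intervention reduction = 0.30 − (4/5) × f × m. Apparent control reduction = f.

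- f = 5%, m = 1: 26% v 5%, difference 21 points instead of 30.
- f = 10%, m = 1: 22% v 10%, difference 12 points.
- f = 10%, m = 0.7: 24.4% v 10%, difference 14.4 points.
- The difference reaches zero at f = 0.30/1.8 = 16.7% (m = 1) or 0.30/1.56 = 19% (m = 0.7).

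**Step 4: the pooled nine-facility total.** With m = 1, a transfer leaves it at 1 − (5 × 0.7 + 4)/9 = 16.7% for every f. With m = 0.7 and f = 10% it is 18.0%. Pure transfers therefore barely touch it. Deaths newly captured from the community do: adding 10% of the control hospitals' baseline deaths (0.4 hospital-equivalents, m = 1) gives 1 − 7.9/9 = 12.2%.

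**Step 5: what assignment by residence does, on the Step 2 inputs.**

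- R = 10, all moved: 35 v 40 + 7 = 47, ratio 0.74. R = 5: 35 v 45 + 3.5 = 48.5, ratio 0.72. Both are close to 0.70, with mild dilution because rerouted control babies benefit from the units.
- R = 10, all from the community, with no such capture in intervention areas: 35 v 50 + 7 = 57, ratio 0.61, which overshoots.
- As above, but with 10 deaths also newly captured from intervention areas: 42 v 57, ratio 0.74 by residence, against (50 + 10 + 10) × 0.7 = 49 v 50, ratio 0.98, by facility.

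Residence removes the misallocation. It does not remove a difference between areas in how completely community deaths are captured.

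**The case against.** The strongest reply is that the primary outcome is not a contrast between arms. It is a before-after count over the same nine hospitals, and a shift between them largely cancels in the total. The passage planning the year-1 comparison names neither an outcome nor a counting rule. This stands, and it makes the concern conditional: it applies if that comparison uses the facility counts, which are the only counting rule for deaths that the article gives. Percentages for individual facilities are distorted in any case.

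A second reply is that many rerouted babies were never going to reach a control hospital. The call centre rationale says over half of births lack skilled attendance, and the section on clinical observations puts the share of babies with complications who present to facilities at 21%. This also stands. A reader might infer that the effect would be hidden or that the severe cases of control areas move wholesale. The documents support neither: the ratio of 1.05 needs every rerouted death to come from a control hospital, and they support only some cases crossing over.

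A third reply is that referral may be local, since the call centre is to advise on the most suitable facility and tells mothers of units close by. But in year 1 no control hospital has an equipped unit. Community health workers' referral counts are collected and cross-checked, though the stated purpose is utilization. The abstraction form and call centre manual are not shown, so a residence field may already exist.

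A reader might also infer that the same flow inflates the outcome on severe admissions. That outcome is a percentage change in the units over the project period, not a contrast between arms, and control hospitals have no equipped unit in year 1. It is a possibility at most.

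**Conclusion.** The concern holds in conditional form. The article's referral rule, the early roll-out of the call centre to control areas and the delayed units together send some control-area babies to intervention hospitals during year 1. A comparison between arms based on deaths or admissions by treating facility would book them to the wrong arm and, for deaths, bias against the intervention.

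The direction follows from the text; the size does not. On the assumed inputs, ten rerouted deaths move a true ratio of 0.70 to somewhere between 0.84 and 1.05, and the bias vanishes as rerouting falls to zero. The pooled before-after total is not undermined by pure transfers. The point is worth correcting because the remedy is cheap and the year-1 comparison cannot be repeated once the control hospitals have units.

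**What to change.** 1. Record the mother's sub-county of residence and the place of birth on the data abstraction form, if they are not already there.
2. State that, for the year-1 controlled comparison, each admission and death is assigned to the catchment of residence whichever hospital treated the baby, with catchment births as denominator where available.
3. Report the facility-based figures as secondary, with the number of cross-catchment referrals beside them.

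The cost is two fields and one analysis rule. Some residence data will be missing. The contrast will be somewhat diluted because referred control-area babies benefit from the units (0.74 instead of 0.70 in the illustration with all ten moved). Differences between areas in how well community deaths are captured will remain and should be acknowledged when the result is read. No change to the referral rule is proposed.

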#### Inputs

Call center manual of operationCalling and texting equipment; Smart phones and computersOffice furnitureCalling creditCall center attendants

#### Outputs

Number of callsNumber of referralsCommunity events based surveillance data fed into the telehealth platformNumber of newborns followed up.Number of expectant mothers followed up and messaged

#### Beneficiaries

Mothers of newbornsNewborns in the communityExpectant women

#### Interphase of telehealth platform and call center

The two innovations, telehealth and call center are key components in the success of the project. These will interphase as follows;The call center will promote community referral system linkage with the community based midwifes and the special care units, promoting utilization of the units. The telehealth platform will enhance the capacity of the clinicians in these units raising standards of care, user satisfaction and ultimately improving neonatal health outcomes.The call center will focus on follow up of the neonates born within the county health care system and without. The follow up data will be uploaded into the telehealth platform allowing the project pediatricians and clinicians understand the situation of the newborns in the community, respond to queries arising during follow up and streamline care and discharge processes in the special care units. See Fig. 1.

**Fig. 1 Fig1:**
[figure not shown]
Interphase of the telehealth platform and the call centre service

#### Privacy, informed consent and confidentiality

Every person’s privacy shall be respected and where they are required to provide information they shall be informed of the purpose for which the information is required, informed of their right to withdraw from the interview at any stage and time, and that information will not be divulged to third parties. Further, the subjects will be informed of the fact that their right to medical attention and other natural privileges will not be affected whatsoever by their agreeing to participate or refusing to participate in the interviews to be conducted. This information will be shared to target subjects in a language understood and where possible in writing.

Subjects will also be informed of the fact that all information collected for the purpose of the study shall solely be used as such and subsequently destroyed after about 3 years following completion of the study. No identifiers will be used such that information collected shall not be linked to the persons who shall have provided such information.

#### Control group

The study ensures that the control group will also receive the full intervention towards the end of the project period so that they do not remain disadvantaged. Initially they shall benefit from community sensitization, tele health platform and call center. After a period of 1 year, the control group will be ready for the full intervention which will include establishment of functional specialized neonatal units.

#### Study assumption

The main assumption in this study is that the intervention and control sites have similar characteristics. Since the facilities are under different Health Facility Management Teams, and health priorities, and decisions made by the HFMT are dependent on the catchment community of each facility, there is a possibility that the intervention and control sites are not necessarily comparable. However, since the sites have low PNC coverage and similar challenges affecting access and utilization of neonatal health services, it is assumed that the differences will not affect the outcome of the study.

## Discussion

The innovation has four components supporting each other as follows;Operation of telehealth platform which is an innovative tool that supports teleconsultations between professional paediatricians and the clinical offices at different health facilities. The telehealth platform essentially provides solution to the challenge of inadequate professionals in the target area which currently has a single paeditrician serving a total population of approximately 1.7 Million people. It enables realtime consultations between the clinical officers and the paeditricians. In addition, it enables professionals in distant locatilities bridge the gap by providing required services. There are 5 professionals from Nairobi (a distance of approximately 500 Kilometers) serving the population in addition to the one resident professional. It works by having the clinical officers take images of newborns under stress and share the same alongside clinical notes with professionals for advice in realtime.Call centre enables the call centre attendants who are trained nurses to consult with mothers of newborns and offer advice aimed at shortening decision making to seek care. This handles the challenge of delayed decisions to seek medical care. The mothers will call the call centre and present any challenges they face with their newborns with an aim of getting advise to handle the danger signs that they may have noted with their newborns. This enables them to make decisions to seek required medical care on time. Community engagement involves sensitizing the community members especially mothers of newborns of improved facilities within their locality. In addition, the community members are trained on how to identify danger signs in newborns and take remedial action in good time. This approach reduces the delay in seeking care for the newborns when required. When the community is sensitized, it becomes proactive and make relatively good decisions concerning the health of their newborns.Measuring results (outputs and outcomes) will involve undertaking a baseline survey to establish benchmarks that will be used to gauge the success of the intervention. This survey will involve the community within the target area, clinicians in selected health facilities and administrators of the health facilities including the County government officials who are legally incharge of the health facilities in the region. Outputs and outcomes will be established through internal and external evaluations which will be conducted at midterm and endterm of the project intervention (see Table 1). These will consider the benchmarks established at baseline to establish change in the situation beased on the intervention. This evaluation will be exhaustive enough and objective to ensure that only results that can be attributed to the intervention will be included since there are many other efforts towards improving the helthcare of newborns in the target area.

## Abbreviations

CICF: County Innovation Challenge Fund
HFMT: Health Facility Management Teams
HMIS: Health Management Information Systems
KDHS: Kenya Demographic and Health Survey
KNBS: Kenya National Bureau of Statistics
OJT: On job training
PNC: Post-Natal Care
WHO: World Health Organisation
